## Abstract

**Background:**

Stress, anxiety, distress, and depression are high among health care workers during the COVID-19 pandemic, and they have reported acting in ways that are contrary to their moral values and professional commitments that degrade their integrity. This creates moral distress and injury due to constraints they have encountered, such as limited resources.

**Objective:**

The purpose of this study is to develop and show the feasibility of digital platforms (a virtual reality and a mobile platform) to understand the causes and ultimately reduce the moral distress of health care providers during the COVID-19 pandemic.

**Methods:**

This will be a prospective, single cohort, pre- and posttest study examining the effect of a brief informative video describing moral distress on perceptual, psychological, and physiological indicators of stress and decision-making during a scenario known to potentially elicit moral distress. To accomplish this, we have developed a virtual reality simulation that will be used before and after the digital intervention for monitoring short-term impacts. The simulation involves an intensive care unit setting during the COVID-19 pandemic, and participants will be placed in morally challenging situations. The participants will be engaged in an educational intervention at the individual, team, and organizational levels. During each test, data will be collected for (1) physiological measures of stress and after each test, data will be collected regarding (2) thoughts, feelings and behaviors during a morally challenging situation, and (3) perceptual estimates of psychological stress. In addition, participants will continue to be monitored for moral distress and other psychological stresses for 8 weeks through our Digital intervention/intelligence Group mobile platform. Finally, a comparison will be conducted using machine learning and biostatistical techniques to analyze the short- and long-term impacts of the virtual reality intervention.

**Results:**

The study was funded in November 2020 and received research ethics board approval in March 2021. The study is ongoing.

**Conclusions:**

This project is a proof-of-concept integration to demonstrate viability over 6 months and guide future studies to develop these state-of-the-art technologies to help frontline health care workers work in complex moral contexts. In addition, the project will develop innovations that can be used for future pandemics and in other contexts prone to producing moral distress and injury. This project aims to demonstrate the feasibility of using digital platforms to understand the continuum of moral distress that can lead to moral injury. Demonstration of feasibility will lead to future studies to examine the efficacy of digital platforms to reduce moral distress.

**Trial Registration:**

ClinicalTrials.gov NCT05001542; https://clinicaltrials.gov/ct2/show/NCT05001542

**International Registered Report Identifier (IRRID):**

DERR1-10.2196/32240

## Introduction

### Background

Health care providers, particularly during the COVID-19 crisis, have reported acting in ways that are contrary to their moral values, integrity, and professional commitments because of constraints in their work environments [1,2]. Moral suffering can ensue when a health care provider’s moral foundation is threatened or violated by witnessing or participating in decisions or actions that degrade their integrity [3]. Moral distress might arise when health care providers are unable to translate their moral choices into action because of internal or external constraints [4].

Moral injury, a more extreme form of moral distress, arises in high-stakes situations wherein integrity and conscience have been violated or one’s moral core is eroded [5]. As these events and other workplace stressors accumulate, health care providers’ capacities to provide the level of care they desire can be diminished. There has been a growing attempt to conceptualize moral distress and injury in different health care professions, but the numerous definitions can confuse the issue [6,7]. The concept of moral injury has existed for much longer than its first conceptualization by Shay [7] concerning the military, where it was defined as a betrayal of moral character, usually as a result of the actions of a person in a position of authority. There is a large body of literature within the military context, and moral injury has conceptually evolved to include betrayal of one’s moral values, and furthermore, as a spiritual, psychological, and somatic response to a series of morally injurious events [5]. While some may contend that actions by military members during a war require forethought based on training, others suggest that actions are made on rapid and subconscious decision-making and that moral injury occurs only when individuals question their actions after the fact [8].

However, moral injury is not well defined in health care professions. Cartolovini et al [9] argue that moral injury occurs in health care providers when they encounter traumatic events that involve high-stakes situations beyond their control in which they perpetuate, fail to prevent, or bear witness to actions that transgress deeply held moral beliefs [10]. A related concept, moral distress, was first described within the nursing context by Jameton [11] as “… when one knows the right thing to do, but institutional constraints make it nearly impossible to pursue the right course of action.” Additional studies [12] have provided more context to this definition and have described causes of moral distress as beyond the organization to specific clinical situations and internal caregiver dynamics. Moral distress and injury likely occur along a continuum, with moral injury at the extreme end [13].

The COVID-19 pandemic has necessitated fundamental changes to health care provision. As we continue to learn about the virus and differing courses of disease, health care providers have often willingly accepted inherent risks during the pandemic to care for their patients. However, the need for rapid and changing contingency planning, shortages in personal protective equipment, resource shortages, and the inability to provide the ethical caring called for by professional codes of ethics have placed health care providers in what has been described as a “war zone [14].” The sudden and unprecedented similarities between civilian health care and military scenarios have potentially resulted in moral distress and possibly moral injury. It is nearly impossible to anticipate the course of the virus and make predictions about its physiological outcomes; it is also challenging to predict the course of mental health needs of health care providers, but it is known that there will be needs.

Research has concentrated on treatment for moral injury, either in the military realm or the civilian realm. Gilligan [15] discussed moral injury as “a shattering of trust that compromised our ability to love” and would seem to suggest the health care providers who suffer moral injury during extreme circumstances such as a pandemic may lose the ability for empathy that is required by professional values. Moral injury has been found to not generally respond to typical treatment of posttraumatic stress disorder, even though most treatment focuses on the posttraumatic stress disorder symptomatology [5]. Being able to preserve or restore integrity requires that health care providers have the opportunity for moral repair by strengthening their moral compass and restoring their integrity. Having a moral compass has been identified as a modifiable factor effective in healing from trauma [16]. When one’s moral foundation is clear and accessible, health care providers have a potential opportunity to heal the wounds caused by the COVID-19 crisis and an additional resource that they can leverage when ethical challenges arise.

In this paper, we propose using digital platforms, specifically virtual reality and mobile apps, to develop an understanding of the continuum of moral distress that leads to moral injury in health care workers. Virtual reality technology will be used as a digital platform to simulate an intensive care unit during the pandemic. Our aim is to determine the feasibility of creating a digital environment and implementing digital interventions to better understand the phenomenon of moral distress by developing platforms to examine moral distress and monitor participants over time in order to develop a better understanding of the continuum of moral distress to moral injury.

## Methods

### Ethics

As of March 20, 2021, the research ethics board at St. Michael’s Hospital, Unity Health Toronto has approved the study, and the reference number is UHTDTS25377. The clinical trial is registered with ClinicalTrial.gov with the Registration/identifier number NCT05001542.

### Overview

We will recruit health care workers to participate in our feasibility trial that will be composed of pretesting, 2D educational video, posttesting, and longitudinal monitoring (Figure 1). During pre- and posttest components, we will pilot unique digital technology platforms (virtual reality environments) to identify circumstances that have the potential to cause moral distress; examine interactions at the individual, team, and organizational levels; perform detailed concept mapping to understand features of moral distress and injury and to aid the design of potential interventions. The educational video will be in 2D; however, the rest of the study components will be 3D virtual reality. The video will be presented on the virtual reality headset after the pretest and before the posttest, and is a brief educational video about moral injury. After the posttest, for 2 months, we will longitudinally monitor participants through the collection of active and passive data through our novel mobile platform.

**Figure 1 figure1:**

Flow diagram of feasibility trial design. VR sim: virtual reality simulation. DiiG: digital intervention/intelligence group.

The expected outcomes of our protocol include (1) using virtual reality technology to design a virtual reality environment to simulate intensive care unit settings during the pandemic and determine the feasibility of understanding moral distress and injury for potential future implementations of digital interventions and (2) using acute physiological monitoring within a virtual reality for simulation of a hospital environment where health care workers have to make challenging moral decisions in complex moral simulated situations, and using a novel mobile platform for longitudinal monitoring by collecting passive and active data to understand the contribution of moral distress to the experience in real-time. The information from these digital platforms will influence each other and aid in the development of models to predict and respond to risks associated with moral distress and injury.

### Experimental Flow

#### Participant Recruitment

Eligible participants include health care providers at 3 affiliated hospitals at Unity Health Toronto, who are 18 years of age or older and who own a mobile phone (Android phones with OS version 6.0 and above, iPhone 6 with OS 11 and above). Since this is a feasibility study conducted among health care providers during a pandemic, we require participants to be currently providing health care at the respective hospitals.

We aim to recruit 15 health care providers (minimum of 10 participants including physicians, nursing, and allied staff) from St. Michael’s, St. Joseph, and Providence hospitals by posting study notices on Unity Health Toronto microsites (eg, Twice a Week newsletters, MD matters, Leadership links), posting flyers at the hospital sites, and by sending email notices. Interested participants will email the study coordinator indicating their interest to participate in the study. The study coordinator will send the participant the consent and demographics forms to sign and complete, and the available time slots to participate in the virtual reality and wearable component of the study. (The demographic survey will include questions regarding age, sex, type of work at Unity Health Toronto, COVID-19 clinical status). Participants will be required to email back their choice for their preferred time slot, the signed consent form, and the completed demographics form.

#### Introduction and Prebrief

The session begins with an introduction of our feasibility trial, goals, and objectives. The session will prepare the participant for the virtual reality simulation in which they take on the role of a health care provider during the COVID-19 pandemic. We will utilize virtual reality simulation to understand the decision-making and emotional response of health care professionals in morally challenging environments, and we will use physiological sensors to monitor the responses. This information will allow us to develop a better understanding of moral distress and create an appropriate intervention.

#### Pretest: Virtual Reality Scenario

After the introduction, participants take on the role of health care providers. The scenario will take place in a hospital setting and will include a physician and nurse, all of whom will be computer-controlled nonplayable characters. There will be an ongoing discussion among them in a scenario that involves decision-making in a morally challenging context.

The virtual reality scenario was created with a particular focus on 2 situations and modified iteratively based on the concepts and research related to moral distress and injury—not having the power to decide which patient to provide life-saving care to when resources are limited and not being able to provide optimum care to all patients.

This pretest virtual reality scenario will initially include all the suggested interventions at the individual, team, and organizational levels and examine the efficacy of these suggested interventions. Additional interventions will be added based on user experience.

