#### Posttest: Virtual Reality Scenario

For the posttest, the virtual reality scenario with moral distress and injury knowledge and its respective interventions are repeated.

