### Compound Intervention

The compound intervention is composed of the virtual reality simulation-based educational intervention and data collection of mental health and moral injury surveys. The virtual reality simulation-based educational intervention contains a moral injury educational video based on the Moral Injury Guide developed by the Ottawa PTSD Center for Excellence [17].

The latter component of the compound intervention evaluates the effectiveness of the virtual reality simulation-based educational intervention through mental health surveys. These surveys include the Perceived Stress Scale (PSS), Moral Injury Outcome Scale (MIOS), Igroup presence questionnaire (IPQ), and Adapted Moral Injury Symptom Scale: Health care Professionals Version (MISS-HP). PSS is a self-report instrument that evaluates level of stress. MIOS and MISS-HP are tools that evaluate the effect of moral injury, and the IPQ is a questionnaire that evaluates the experience of presence during virtual reality simulations. We will use this information to improve our compounded intervention for use on digital platforms iteratively.

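### The change from first to second run of one scenario in a single cohort cannot be attributed to the video, and the efficacy of the embedded interventions cannot be estimated

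*Protocol article*

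**What the plan says.** The Abstract (Methods) describes a "prospective, single cohort, pre- and posttest study" and gives its purpose as "examining the effect of a brief informative video describing moral distress on perceptual, psychological, and physiological indicators of stress and decision-making". It mentions one "virtual reality simulation that will be used before and after the digital intervention for monitoring short-term impacts". The Overview places the video between pretest and posttest, and Trial Design describes a single in-person session.

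Under Pretest: Virtual Reality Scenario the article says: "This pretest virtual reality scenario will initially include all the suggested interventions at the individual, team, and organizational levels". The same paragraph gives the pretest the task of examining the efficacy of these interventions, and allows more to be added in response to user experience. The Intervention section names the video as the intervention and says that it summarizes interventions at the same three levels. Under Posttest: Virtual Reality Scenario, "the virtual reality scenario with moral distress and injury knowledge and its respective interventions are repeated".

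Tables 1 and 2 show a fixed script that includes a ventilator removal, a cardiac arrest and a closing scene of counsel from a senior physician.

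Compound Intervention says that the survey component "evaluates the effectiveness of the virtual reality simulation-based educational intervention through mental health surveys". The Abstract (Conclusions) takes a different line: "Demonstration of feasibility will lead to future studies to examine the efficacy of digital platforms to reduce moral distress". The Discussion also leaves efficacy to later work.

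**The concern.** The target in the Abstract is the effect of the video. With one arm, the only within-session evidence on it is the difference between the second and first runs. On the second run participants have seen the video, but they also know the script, its outcome and the supportive scene. A lower stress response could come from any of these.

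Two stated aims are at stake. The effect of the video is mixed with repeat exposure. The efficacy of the embedded interventions has no comparison at all, because they are present in both runs. A change reported as an effect of the video could mislead the design of the larger study that the Discussion foresees.

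**Working it through.** The article gives no effect size, standard deviation, alpha or power, so there is no planned figure to reproduce. The main check is algebraic; the numbers after it are only an illustration.

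**1. What the contrast contains.** Define, for a within-session measure:

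- B: response to the scenario without interventions
- I: effect of the interventions embedded in the scenario
- V: effect of the video
- R: effect of repeating a known scenario in the same session (habituation, practice, known outcome, elapsed time, regression to the mean)
- C: carry-over from interventions met in the first run

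Then:

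- pre = B + I (Pretest section)
- post = B + I + V + R + C (Posttest section)
- post − pre = V + R + C

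One arm gives one equation in three unknowns. More participants narrow the interval around the sum but do not isolate V.

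**2. The embedded interventions.** I appears in both runs and cancels. This has two consequences:

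- If the interventions are identical in both runs and additive, they do not bias the contrast for V.
- Their own efficacy cannot be estimated, because that needs a run consisting of B alone.

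Two passages put the cancellation in doubt. The Pretest section lets interventions be added. The Posttest wording about moral distress and injury knowledge could mean either what participants now know or extra posttest content. If content changes between a participant's two runs, the change in I enters the contrast. If it changes between participants, I differs among them.

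**3. How large the problem could be.** Inputs from the article: n = 15 as target and 10 as minimum (Participant Recruitment). Assumed, with no source in the article: V = 0; a repeat-exposure shift h of 0.3 or 0.5 SD; pre-post correlation r of 0.5 to 0.8; a two-sided 5% paired t-test. The standardized paired difference is dz = h / √(2(1 − r)) and the noncentrality is dz × √n.

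- h = 0.3, r = 0.5: dz = 0.3 / √1.0 = 0.300
- h = 0.3, r = 0.8: dz = 0.3 / √0.4 = 0.474
- h = 0.5, r = 0.5: dz = 0.5 / √1.0 = 0.500
- h = 0.5, r = 0.8: dz = 0.5 / √0.4 = 0.791

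Probability of p < 0.05 from the noncentral t distribution:

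| n | h (SD) | r = 0.5 | r = 0.8 |
|---|---|---|---|
| 15 | 0.3 | 0.192 | 0.402 |
| 15 | 0.5 | 0.438 | 0.812 |
| 10 | 0.3 | 0.136 | 0.269 |
| 10 | 0.5 | 0.293 | 0.606 |

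The nominal rate is 0.05. These figures do not predict what this trial will find.

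**The case against.** The strongest reply is that this is openly a single-cohort feasibility study. Its size is justified by feasibility and availability of staff, and efficacy is left to later work. The article specifies no paired t-test and no efficacy threshold; its analysis sections plan feature extraction and classification. This stands. It lowers the severity and confines the error rates above to illustration. It does not remove the stated aims of effect, efficacy and effectiveness, which conflict with the deferral.

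A reader might infer that the pretest is contaminated because it already contains the interventions under test, so that the baseline spoils the video contrast. The documents do not support that. The Posttest section repeats the same interventions, and using one scenario in both runs is what a pre-post comparison needs. The video itself is not in the pretest. That the embedded content shrinks a true video effect is possible but not shown. Nor is every baseline already treated: Trial Design collects survey data in the prebrief, and Subjective Data Collection places the MIOS and PSS at the beginning and end of the study.

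It is also tempting to strip the interventions from the pretest alone. That would make post − pre = I + V + R, so that the runs would differ by more than the video. Stripping them from both runs would leave R untouched.

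Finally, the three claims have different objects. Only the Abstract speaks of the video alone. The Pretest section concerns the embedded interventions, and Compound Intervention concerns the whole simulation-based educational package. One replacement sentence would not fit all three.

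**Conclusion.** The point holds in a limited form. The within-session change estimates video plus repeat exposure plus carry-over, so the effect of the video named in the Abstract is not identifiable at any sample size. The efficacy aim in the Pretest section cannot be met because no run omits the interventions. Neither conclusion depends on the assumed numbers. The statement that the embedded interventions leave the video contrast unbiased rests on their being identical in both runs and additive.

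Under the assumptions in the working, a false attribution to the video could occur in 19% to 40% of trials at 0.3 SD and 44% to 81% at 0.5 SD with 15 participants, and in 14% to 27% and 29% to 61% with 10. The article gives no evidence on the size of a repeat-exposure shift in this setting.

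The feasibility aims are unaffected. What changes is what the trial may conclude from its pre-post comparison.

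**What to change.** - **Abstract, Methods:** describe the within-session result as change from first to second exposure (video plus repeat exposure). Report it as an exploratory paired change with a 95% CI, and do not attribute it to the video.
- **Pretest section:** delete the aim of examining the efficacy of the embedded interventions. State that scenario content is the same in both runs of each participant, and record any version change between participants.
- **Posttest section:** state whether the moral distress and injury knowledge is what participants bring from the video or added content, so that it agrees with the Pretest and Intervention sections.
- **Compound Intervention:** replace the claim to evaluate effectiveness with an exploratory description of uncontrolled change in survey scores, in line with the Abstract (Conclusions) and the Discussion.

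The cost is wording, a version record and a more modest headline claim. No new arm or scenario is needed. Isolating the video's effect would need a comparison that this design does not have, and belongs in the later studies that the article foresees.
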